In this study, the sample will include adolescents with chronic pain and one of their parents. Based on a within-subjects repeated measures ANOVA with three time points (baseline, post-treatment, and 3-month follow-up), we will use GPower (version 3.1.9.7) to calculate the required sample size. We set a small effect size (f = 0.10), with a two-tailed alpha of 0.05 and power of 0.80. For the calculation, the following parameters were assumed: number of measurements = 3 (baseline, post-treatment, and 3-month follow-up), correlation among repeated measures = 0.5, and nonsphericity correction epsilon = 1. This calculation indicated that a sample of *N* = 163 dyads would be sufficient. However, in order to prevent attrition issues, we will be recruiting a minimum of 195 dyads -minimal attrition is expected based on prior studies on digital treatments with similar populations (37). Recruitment is expected to proceed at a rate of approximately 5 participants per month, based on projections from similar previous studies [e.g., (30)]. To account for potential variability, we conservatively estimate a recruitment rate of 2 adolescents per month per hospital. With 8 hospitals participating, this would result in enrolling the required sample of 352 participants within 22 months. An additional 5 months will be allocated for participants to complete the treatment (approximately 8 weeks, as previously described) and the 3-month follow-up, bringing the total duration for recruitment, enrollment, and follow-up to 27 months.

In order to ensure that the target sample size is reached in the evaluation study, the following strategies will be implemented: (a) using clear and engaging messages (i.e., developing age-appropriate, visually appealing recruitment materials, like posters, flyers, or videos to be shared by hospitals and healthcare professionals); and (b) highlighting the benefits of participation, such as improving their own pain management and contributing to advancements in adolescent healthcare. Moreover, we will offer both monetary and non-monetary incentives (i.e., certificates of participation and feedback on their progress). To enhance participant retention and ensure completion of follow-ups, we plan to implement personalized reminders. These reminders will be delivered via app notifications, SMS, or email, and will serve to notify participants of upcoming tasks or scheduled follow-up activities.

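### The evaluation study gives two incompatible sample sizes (at least 195 dyads, and 352 participants) and two accrual rates, and its 22- and 27-month schedule does not follow from the 195-dyad target

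*Protocol article*

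**What the plan says.** All the relevant text is in one paragraph of section 2.3 (Participants) of the protocol article.

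- **Design and inputs.** "Based on a within-subjects repeated measures ANOVA with three time points (baseline, post-treatment, and 3-month follow-up"; "We set a small effect size (f = 0.10), with a two-tailed alpha of 0.05 and power of 0.80"; "correlation among repeated measures = 0.5, and nonsphericity correction epsilon = 1".
- **Result.** The calculation returns 163, which the article says "dyads would be sufficient". A dyad is one adolescent and one parent.
- **Recruitment target.** "we will be recruiting a minimum of 195 dyads -minimal attrition is expected based on prior studies". No attrition rate is given.
- **Accrual rate.** About 5 participants per month is expected, from similar earlier studies. A rate of 2 adolescents per hospital per month is then adopted and described as conservative.
- **Second sample size and schedule.** "With 8 hospitals participating, this would result in enrolling the required sample of 352 participants within 22 months". Five further months for treatment and follow-up are added, "bringing the total duration for recruitment, enrollment, and follow-up to 27 months".

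**The concern.** The paragraph sets a minimum of 195 dyads and then, for the same study, names 352 as what is required. Nothing links the two. A reader cannot tell which number ends recruitment, and 352 is 157 more than 195, or 81% (157/195). The participants are minors enrolled with a parent, and the article gives no statistical reason for the additional families.

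The accrual and total durations are built on 352, so they inherit the problem. The two accrual rates add a second inconsistency: a conservative rate should be lower than the expected one, yet here it is about three times higher. Correcting the target alone would still leave the duration undetermined.

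**Working it through.** **1. Reproduce the plan's own figure.** Inputs from section 2.3: f = 0.10, m = 3 measurements, ρ = 0.5, ε = 1, α = 0.05, one group. For the within-subjects effect:

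- λ = f² × N × m × ε / (1 − ρ) = 0.01 × N × 3 / 0.5 = 0.06 N
- df₁ = (m − 1)ε = 2; df₂ = (N − 1)(m − 1)ε = 2(N − 1)
- power = P(noncentral F > critical F at α)

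| N analysed | λ | Power |
|---|---|---|
| 162 | 9.72 | 79.98% |
| 163 | 9.78 | 80.2% |

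The figure of 163 reproduces exactly.

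**2. Attrition allowance.** 1 − 163/195 = 16.4%. This rate is implied, not stated.

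**3. Where 352 comes from.** 8 × 2 × 22 = 352 exactly. It is an accrual projection that counts adolescents.

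**4. Attempts to reconcile 352 with the calculation.**

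- *Individuals instead of dyads:* 163 dyads are 326 people and 195 dyads are 390. Conversely, 352 people are 176 dyads, below the stated minimum of 195.
- *Attrition:* 1 − 163/352 = 53.7% loss, against an expectation of minimal attrition.
- *Other inputs, changed one at a time:* ρ = 0 gives 323; ε = 0.5 gives 264; α = 0.025 gives 194; power 0.95 gives 259; power 0.99 gives 359. None gives 352.

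**5. Durations.** Accrual = target / rate; total = accrual in whole months + 5.

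| Target | Rate per month | Accrual (months) | Total (months) |
|---|---|---|---|
| 352 | 16 | 22 | 27 (as stated) |
| 195 | 16 | 12.2, so 13 | 18 |
| 195 | 5 | 39 | 44 |
| 352 | 5 | 70.4, so 71 | 76 |

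Only 352 at 16 per month returns 22 and 27. If the 5 were meant per hospital (5 × 8 = 40 per month), 16 would indeed be conservative, but the text does not say so, and 195 at 16 per month would still not take 22 months.

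**6. Power at each target, allowing for attrition.** Applying the implied retention 163/195 = 0.836 to both:

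- 195 enrolled leaves 163 analysed: 80.2%.
- 352 enrolled leaves 352 × 0.836 ≈ 294 analysed: 97.1%.

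With no attrition at all the figures would be 87.2% and 98.9%.

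**The case against.** The best defence is that 195 is only a minimum, so enrolling more is allowed, and that both numbers exceed the 163 the calculation asks for. The second half stands: under the plan's own assumptions neither target leaves the study short of power. The first half does not remove the contradiction, because 352 is presented as required, not as a ceiling or a projection of what the sites could deliver.

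Four stronger readings are tempting, and the article supports none of them.

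- *The sample size calculation is wrong.* It is not; it reproduces to the unit.
- *352 is a slip and should be deleted.* That may be so, but the word minimum leaves a larger target open, and the choice is the sponsor's. What can be said is that 195 is the only recruitment target the article supports.
- *The true duration is 18 months.* That holds only at 16 per month. At the other stated rate it is 44, so printing 18 would put one unsupported duration in place of another.
- *The team means to look at the data at 195 and decide whether to go on.* Nothing says this. Section 2.2.4 mentions sharing preliminary findings with clinicians, but to sustain their interest, not to govern stopping. Two targets leave that possibility open; they do not show it is planned.

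Figure 3 and the registry entry are not available here, so whether either carries 195, 352 or another number is unknown.

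**Conclusion.** Wrong as written. Section 2.3 names two targets that cannot both be the required sample, and the larger, 81% above the smaller, has no derivation. The 22-month accrual and 27-month total follow from 352 at 16 per month and from no other pairing of a stated target with a stated study-wide rate. For 195 dyads the total is about 18 or 44 months, according to which rate is meant. The 5 months for treatment and follow-up do not depend on 352 and are not in question.

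The conclusion rests on the article's own inputs. It assumes that the 5 per month is a study-wide rate, as the text reads, and that each recruited adolescent brings one dyad. The power figures of 80.2% and 97.1% assume the implied 16.4% loss applies at either target. The validity of the analysis is not affected. The defect is that the enrolment commitment is contradictory and the schedule is built on its unsupported half.

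**What to change.** In section 2.3:

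1. State one enrolment target with its derivation. If it is 195 dyads, give the attrition rate that links 163 to 195. If 352 is intended, give the calculation that produces it and say whether it counts adolescents, dyads or individuals.
2. State one accrual rate with its unit (per study or per hospital). If an expected and a cautious rate are both kept, make them consistent.
3. Recompute accrual and total duration from that target and rate.
4. State that enrolment closes at the target regardless of any results seen during the study.

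Then check the projected numbers in Figure 3 and the registry entry against the chosen target, and correct them if they differ.

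The cost is a few sentences in section 2.3 and possibly a figure and registry update. If the target is 195, no additional families are needed. If it is 352, the cost is justifying a sample 157 larger than the one now supported. If the 5-per-month rate is the realistic one, the schedule lengthens well beyond 27 months, which the sponsor needs to know before committing sites.

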### Outcomes and measures

2.4

The outcomes used are based on the recommendations of a recent consensus study involving several stakeholders [children with chronic pain, parents, healthcare experts and researchers; (38)]. The main outcomes of the evaluation study are pain intensity, pain interference and the global impression of change after treatment. In addition, we will collect information from a group of secondary outcomes. To capture the overall impact of the intervention, we will assess global impression of change using a standardized measure as suggested in the Core Outcomes in Pediatric Persistent Pain Workgroup (39).

Both adolescents and their parents will respond to an online survey including questions about sociodemographic characteristics, concomitant treatments and pain medication (type and doses). In addition, adolescents will complete the following outcome measures: pain intensity [NRS-11; (40)], pain interference [PROMIS Pediatric Pain Interference; (41)], pain-related self-efficacy [PSEQ; (42)], concerns about pain [UW-CAP; (43)], pain attitudes [Peds-SOPA; (44)], functional disability [FDI; (45)], anxiety [PROMIS Pediatric Anxiety; (46)], depressive symptoms [PROMIS Pediatric Depression; (46)], sleep disturbance [PROMIS Pediatric Sleep disturbance; (47)], fatigue [SFS; (48)], treatment expectancies (49), treatment perceptions [perception of how easy to use and how helpful the skills taught are; (50)], adherence (i.e., use of DigiDOL-Ad and of the skills learned with treatment), global impression of change after treatment (38), satisfaction with treatment (51) and adverse effects (52).

In addition, the parents' online survey will include the following outcome measures: functional disability [FDI; (45)], treatment expectancies (49), satisfaction with treatment (51), and global perception of change after treatment (38). Figure 2 provides details of the SPIRIT schedule of enrolment, intervention and assessments.

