### Limitations

3.2

The key challenges anticipated in this project are related to (1) recruitment and inclusion of participants in the different studies, due to abandonment of a clinician/chronic pain program, and the difficulty to involve stakeholders in the FGs and usability studies; (2) privacy and data protection issues; (3) as a digital intervention, potential technical difficulties or poor usability could affect participants engagement; and (4) the content on companion websites for parents and teachers might be misunderstood, leading to unintended consequences. The mitigation actions (*contingency plan*) addressed to solve recruitment issues are as follows, depending on the causes: (a) monitoring constantly the involvement of clinicians, having a close and continued relationship with them (in relation to this, we have planned to send monthly updates to clinicians, and award a prize to the program providing the highest number of referrals), and (b) the Principal Investigator, in ongoing meetings with all stakeholders, will inform them on the project to raise interest and gain trust in the outcomes of the research proposal. In relation to (2) privacy data issues, we plan that the data collected during the implementation process will not leave the local secure networks where the data will be hosted at the university premises. Moreover, in relation to technical and usability issues, we have planned iterative usability testing phases and will provide dedicated technical support to identify and resolve any issues promptly. Finally, in relation to misinterpretation of information, the content will be developed in consultation with experts, and clear guidelines for interpretation and use will be provided.

Finally, another limitation of this project is the use of a single-group design to study the treatment. Without a control group for comparison, it is challenging to determine whether the observed outcomes are genuinely attributable to the treatment or influenced by external factors such as the placebo effect, natural progression of the condition, or other variables. If the evaluation study demonstrates positive results, a randomized controlled trial will be conducted in the future to validate and strengthen the findings.

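### Three unranked main outcomes are set against a sample size worked out for one unnamed ANOVA at 0.05, so the stated error rate and power describe only one of them

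*Protocol article*

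**What the plan says.** Section 2.4 (Outcomes and measures): "The main outcomes of the evaluation study are pain intensity, pain interference and the global impression of change after treatment". The next sentence separates these from the rest: "In addition, we will collect information from a group of secondary outcomes". The three therefore share the top rank, and none is called primary.

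Section 2.3 (Participants) bases the sample size on one within-subjects ANOVA with three time points: "We set a small effect size (f = 0.10), with a two-tailed alpha of 0.05 and power of 0.80". It also assumes "correlation among repeated measures = 0.5, and nonsphericity correction epsilon = 1", and concludes that "163 dyads would be sufficient", with at least 195 to be recruited to allow for attrition. The outcome behind this calculation is not named.

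Section 2.5 (Data analysis) plans ANOVAs in the plural and refers back to section 2.3 for them. It gives no order of testing and no division of alpha. Hypothesis 3 in section 1.1 expects statistically significant improvement in broad domains without tying it to one outcome.

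Section 3.2 (Limitations) attaches a consequence: "If the evaluation study demonstrates positive results, a randomized controlled trial will be conducted in the future". What counts as positive is not defined.

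**The concern.** An alpha of 0.05 and a power of 0.80 are properties of one test. With three outcomes of equal rank, what they mean for the study depends on a success rule that the article does not give. If any one significant outcome may be read as success and each is tested at 0.05, the chance of a false success exceeds 5%. If more than one must succeed, the chance of true success is below the power of the single test. If alpha is divided, power per outcome falls below 80% at the planned number.

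At stake is how the evaluation may be read. Success could be claimed on whichever main outcome turns out significant, and a later randomised trial is said to follow from success.

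**Working it through.** **Inputs.** From section 2.3: f = 0.10, alpha = 0.05, power = 0.80, m = 3 measurements, correlation among repeated measures ρ = 0.5, ε = 1, N = 163, recruitment 195. From section 2.4: three main outcomes. The correlation between outcomes is not given, so a range of 0 to 0.9 is assumed.

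**1. Reproducing 163.** For one group and a within-subjects factor:

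- λ = f²·N·m·ε/(1−ρ) = 0.01 × 163 × 3 × 1/0.5 = 9.78
- df1 = (m−1)ε = 2; df2 = (N−1)(m−1)ε = 162 × 2 = 324
- Power from the noncentral F at alpha 0.05 = 0.802. At N = 162 it is 0.7998.

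So 163 is the smallest N that reaches 80%, for one test at 0.05.

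**2. False positives if each outcome is tested at 0.05.**

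- Three independent tests: 1 − 0.95³ = 0.143
- Two independent tests: 1 − 0.95² = 0.0975
- Three correlated tests, simulated under no change at N = 163: about 13.7% at correlation 0.3, 12.7% at 0.5, 11% at 0.7 and 8.6% at 0.9

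The two-test figure matters because global impression of change after treatment has no baseline value. The three-time-point ANOVA therefore fits at most pain intensity and pain interference.

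**3. Power per outcome if alpha is split (Bonferroni), same noncentral F.**

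| Alpha per test | N = 163 | N = 195 (no dropout) |
|---|---|---|
| 0.05 | 80.2% | 87.2% |
| 0.05/2 = 0.025 | 71.5% | 80.4% |
| 0.05/3 = 0.0167 | 66.2% | 75.9% |

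With the three-way split, 80% per outcome needs 212 analysed dyads. The plan's own allowance is 1 − 163/195 = 16.4%, which makes this about 212/(163/195) = 254 recruited.

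**4. Power if both continuous outcomes must succeed at 0.05 each.** With f = 0.10 on each and N = 163: 0.802² = 0.64 if independent, rising to about 0.75 at correlation 0.9.

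**5. Power if any one of three suffices after a Bonferroni split.** With f = 0.10 on each and N = 163: 1 − (1 − 0.662)³ = 0.96 if independent. By simulation it is about 88% at correlation 0.5, 83% to 84% at 0.7, and 76% at 0.9. Steps 3 and 5 treat all three outcomes as if the ANOVA applied to them, so for global impression of change they are only indicative.

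**The case against.** **Error and power are not incompatible.** A reader might infer that 5% error and 80% power cannot both hold with three main outcomes. The document does not support that. A Bonferroni split with any one success sufficient holds familywise error at 5% and gives 96% power for at least one success if the outcomes are independent. This falls below 80% only at very high correlation. Fixed-order testing also keeps 5% error and full power for the first test. What stands is narrower: no such rule is stated, and the figures given belong to one unnamed outcome.

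**The rule may be in a SAP.** Multiplicity rules are often left to one, and this is a condensed article. That answers a complaint about missing detail. It does not answer the choices that the article itself makes: three equal outcomes, one alpha and one N. An alpha split added later would lower power per outcome below the stated 80% at 163.

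**The study is partly about feasibility.** Sections 3.1 and 3.2 stress feasibility and usability and concede that a single group cannot establish attribution. The sentence about a future trial is a discussion remark, not a formal decision rule. This limits the weight of the point. Yet the article still gives a formal power calculation and a hypothesis of significance.

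**Two further tempting figures do not hold.** Joint power for a baseline to post-treatment contrast cannot be derived, because f = 0.10 over three time points does not fix that contrast; it depends on an unstated pattern of means. The 66% and 76% are Bonferroni figures and should not be given as power under Holm, which averages about 72% to 75% per outcome at 163 if all three outcomes have f = 0.10.

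**Section 2.3 also names 352 as the required sample.** At 352 the three-way Bonferroni power would be 96.9%. But the stated calculation supports only 163, and that conflict must be reconciled on its own.

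**Conclusion.** The point holds as a mismatch between the list of main outcomes and the test that was sized. The 80% power is correct for one outcome with three measurements, tested at 0.05, and for nothing more. Testing as written gives a chance of at least one false-positive main outcome of 14.3% under independence (about 9% to 14% over the assumed correlations), or 9.75% for the two outcomes that the ANOVA fits. Dividing alpha by three leaves 66% power per outcome at 163 and 76% at 195. Requiring both continuous outcomes gives about 64% to 75% at 163.

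These results rest on f = 0.10 for every outcome, on the plan's own ρ and ε, and on an assumed range for the correlation between outcomes. They do not show that the design is unable to control error with adequate power. They show that the article has not chosen a rule under which its figures apply. The matter should be corrected, but it is less serious for inference than the lack of a control group, which the article acknowledges.

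**What to change.** Name pain intensity or pain interference as the single primary outcome, tested with the three-time-point ANOVA at 0.05. This keeps 163 and 195 valid. A primary test at post-treatment alone would not match the calculation and would need its own power figure. Then test the other of these two, and after it global impression of change, using a test suited to an outcome without a baseline. Take each step only if the previous one is significant.

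If the three are to stay co-equal, use Holm and state 66% at 163 and 76% at 195 as lower bounds on power per outcome for those analysed by the ANOVA.

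In either case, define in section 3.2 what counts as a positive result by the same rule.

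The cost is a few sentences and a registry update, with no added recruitment under the fixed order. The downside is that outcomes later in the order may not be formally claimed. The 163/195 and 352 figures in section 2.3 need separate reconciliation.

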**Figure 2 F2:**
[figure not shown]
Schedule of enrolment, intervention and assessments for phase 4. t_1_ = enrollment; t_1_ = pre-treatment assessment_;_ t_1.1−1.8_ = weekly check-ins; t_2_ = post-treatment assessment; t_3_ = 3-month follow-up assessment.

Our data management plan prioritizes the privacy and anonymity of participants. To ensure anonymity, participants will be identified in evaluation questionnaires and data analyses using a numerical code. Specialized data protection measures, including password protection, will be implemented as needed to safeguard sensitive information. All collected data will be stored in a password-protected database, accessible exclusively to authorized members of the research team. Data will be processed in aggregate form and used solely for scientific research purposes.

Data will be collected using the platform REDCap and stored in secure servers located at University Rovira i Virgili. Only the Principal Investigator will have access to the data, and he will give access to study personnel, when appropriate for analysis and report writing. Once the study is finished, anonymized data will be available at the repository CORA.RDR, which is an online platform designed for storing and sharing research data supported by the Department of Research and Universities of the Government of Catalonia. Figure 3 provides a Consort diagram (the numbers presented are based on predictive estimates derived from our initial enrollment and attrition forecasts. We have made every effort to ensure these figures are as realistic as possible, but they remain projections and may change once actual recruitment and follow-up data become available).

